- *Equity* will be assessed by comparing retention rates between adults and adolescents and men and women.
- *Patient-centeredness* will be assessed through comparison of means in the results of appropriate dimensions in the semi-structured patient exit-survey.

*c. Patient Outcomes*

- HIV RNA: we compare the proportion of patients suppressed at one year among those exposed to the intervention and control conditions using mixed effects logistic regression
- Satisfaction: we will compare the effect of the intervention on patient satisfaction through mixed effects linear regression.

1. *Sample Size Considerations*

- CAG/UAG: Existing program data suggest that 65% of patients are at least 7 days late for a pharmacy refill visit during their first year in HIV care after starting ART and that 95% of clinics fall within 15% (that is 50 to 80) of this estimate. Thus, a conservative matched co-efficient of variation is estimated to be 0.10. We assume a 50% reduction in missed pharmacy visits due to CAG and UAG. Under these assumptions, for the CAG intervention, our selection of five clinics and 120 patients per site (in 20 CAGs per site assuming complete enrollment), the study will be powered at 96%. Under more conservative assumptions about between clinic variability and the effect size (Appendix 6) this sample size yields power of over 80%. For the UAG intervention, our target sample size is 4 UAGs at each of the five intervention sites with 30 people in each UAG and therefore 120 participants per site (total of 600 participants across sites). Under the same assumptions about coefficient of variation and the effect size as for the CAG model, this sample size yields power of > 90% and is robust to varying assumptions about correlation (See Appendix 6).
- Fast-track: Our target sample size for Fast-track is 200 patients at each of four sites (two intervention sites and two control sites; n=800 total). Assuming baseline 80% of patients miss a pharmacy visit in a year of care, which we anticipate will fall to 40%, we have 80% power.
- START: Assuming ART initiation at 2 weeks rises from 60% to 85%, 100 patients at each of eight sites (four intervention and four control sites; n=800 total), rho of 0.15 yields an anticipated power of 78%. No more than 200 patients will be enrolled into the study to receive POC CD4 testing with their consent. Enrolment will stop when we reach 100 patients who are eligible for ART initiation.

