## 7.6 Appendix 6: Power calculations for Objective 2: CAG and UAG

| Alpha | Pi0 | Pi1 | K | J | N | Power |
| --- | --- | --- | --- | --- | --- | --- |
| **Modify Pi0 and Pi1** |  |  |  |  |  |  |
| 0.05 | **0.8** | **0.6** | 0.1 | 30 | 5 | 0.62 |
| 0.05 | **0.8** | **0.4** | 0.1 | 30 | 5 | 0.997 |
| 0.05 | **0.7** | **0.5** | 0.1 | 30 | 5 | 0.63 |
| 0.05 | **0.6** | **0.4** | 0.1 | 30 | 5 | 0.66 |
| 0.05 | **0.6** | **0.3** | 0.1 | 30 | 5 | 0.96 |
| 0.05 | **0.4** | **0.2** | 0.1 | 30 | 5 | 0.7989 |
|  |  |  |  |  |  |  |
| **Modify k** |  |  |  |  |  |  |
| 0.05 | 0.6 | 0.3 | **0.1** | 30 | 5 | 0.96 |
| 0.05 | 0.6 | 0.3 | **0.2** | 30 | 5 | 0.82 |
| 0.05 | 0.6 | 0.3 | **0.3** | 30 | 5 | 0.597 |
|  |  |  |  |  |  |  |
| **Modify j** |  |  |  |  |  |  |
| 0.05 | 0.6 | 0.3 | 0.1 | **10** | 5 | 0.64 |
| 0.05 | 0.6 | 0.3 | 0.1 | **15** | 5 | 0.7988 |
| 0.05 | 0.6 | 0.3 | 0.1 | **30** | 5 | 0.96 |
| 0.05 | 0.6 | 0.3 | 0.1 | **45** | 5 | 0.991 |
| 0.05 | 0.6 | 0.3 | 0.1 | **90** | 5 | 0.999 |
| 0.05 | 0.6 | 0.3 | 0.1 | **120** | 5 | 0.999 |
|  |  |  |  |  |  |  |
| **Modify n** |  |  |  |  |  |  |
| 0.05 | 0.6 | 0.3 | 0.1 | 30 | **5** | 0.96 |
| 0.05 | 0.6 | 0.3 | 0.1 | 30 | **6** | 0.99 |
| 0.05 | 0.6 | 0.3 | 0.1 | 30 | **7** | 0.997 |

alpha= significance level

Pi0= baseline proportion

Pi1=post-intervention proportion

k=co-efficient of variation

j= sample size per cluster

n= number of matched cluster

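### Protocol 3.2.5 attaches the 96% power of Appendix 6's 30-per-clinic row to 120 patients per site, and the appendix does not show the claimed robustness for 120 per site

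*Protocol*

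**What the plan says.** Section 3.2.5 takes its baseline from programme data: "Existing program data suggest that 65% of patients are at least 7 days late for a pharmacy refill visit" in the first year after starting ART. It assumes that the intervention halves this (0.65 to 0.325), with a matched coefficient of variation k of 0.10. For CAG, with five clinics, it states "120 patients per site (in 20 CAGs per site assuming complete enrollment), the study will be powered at 96" percent. It adds: "Under more conservative assumptions about between clinic variability and the effect size (Appendix 6) this sample size yields power of over 80" percent. For UAG, also at five sites with 120 participants each, it states that "this sample size yields power of > 90% and is robust to varying assumptions about correlation (See Appendix 6").

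Appendix 6 is the support cited. Its columns are alpha, Pi0, Pi1, k, j (sample size per cluster), n (matched clusters) and power. Three rows matter most:

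- "0.05 | 0.6 | 0.3 | 0.1 | 30 | 5 | 0.96"
- "0.05 | 0.6 | 0.3 | 0.1 | 120 | 5 | 0.999"
- "0.05 | 0.6 | 0.3 | 0.3 | 30 | 5 | 0.597"

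No row has Pi0 = 0.65. Outside the block that varies j itself, every row has j = 30.

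**The concern.** The text and the appendix give two different powers for the same planned size. A reader who follows the citation finds 0.96 against 30 per cluster and 0.999 against 120.

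The second problem is the assurance. The sentence on more conservative assumptions speaks of the planned 120 per site, but the rows it points to were all run at 30. As printed, the six less favourable rows (four 20-point effects and two larger values of k) read 0.62, 0.63, 0.66, 0.7989, 0.82 and 0.597, and only the k=0.2 row exceeds 80%. The reader cannot tell from the appendix whether the claim holds at 120.

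This is the sample size justification for both randomised comparisons. With five matched pairs, the main threat to power is variation between clinics combined with an effect smaller than assumed. The text suggests that this has been examined at the planned size, and it has not.

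**Working it through.** **Inputs.** From section 3.2.5: Pi0 = 0.65, Pi1 = 0.325, k = 0.10, 5 matched clusters, 120 per cluster. From Appendix 6: alpha = 0.05 and the tabulated values of Pi0, Pi1, k and j. The appendix does not give the sidedness of alpha or name its formula. The two-sided matched-pair formula below is inferred because it reproduces the table.

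**Formula.** V = Pi0(1−Pi0)/j + Pi1(1−Pi1)/j + k²(Pi0² + Pi1²); power = Φ( √[(n−2)(Pi0−Pi1)²/V] − 1.96 ).

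**Step 1: reproduce the plan's figure.** For 0.6 to 0.3, k=0.1, j=30, n=5:
- V = (0.24 + 0.21)/30 + 0.01 × (0.36 + 0.09) = 0.0150 + 0.0045 = 0.0195
- √(3 × 0.09/0.0195) = 3.721; 3.721 − 1.96 = 1.761; power = 0.961

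This is the 0.96. All 15 distinct Appendix 6 rows come out within one point of the printed value.

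**Step 2: the planned 120 per site.**
- 0.6 to 0.3, k=0.1: V = 0.00375 + 0.0045 = 0.00825; √(0.27/0.00825) = 5.721; power = 0.9999, matching the printed 0.999.
- 0.65 to 0.325, k=0.10: V = 0.00372 + 0.00528 = 0.00900; √(3 × 0.1056/0.00900) = 5.93; power above 0.999.
- The text's effect at 30 per cluster gives 0.977, so the different baseline does not explain 96% either.

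**Step 3: one assumption changed at a time, five pairs.**

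| Pi0 to Pi1 | k | Power at 30 (Appendix 6) | Power at 120 (recomputed) |
|---|---|---|---|
| 0.6 to 0.3 | 0.2 | 0.82 | 0.941 |
| 0.6 to 0.3 | 0.25 | not tabulated | 0.829 |
| 0.6 to 0.3 | 0.3 | 0.597 | 0.695 |
| 0.8 to 0.6 | 0.1 | 0.62 | 0.851 |
| 0.7 to 0.5 | 0.1 | 0.63 | 0.905 |
| 0.6 to 0.4 | 0.1 | 0.66 | 0.951 |
| 0.4 to 0.2 | 0.1 | 0.7989 | 0.997 |

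With 0.65 to 0.325 at 120, k=0.2 gives 0.946 and k=0.3 gives 0.701.

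At k=0.3 (0.6 to 0.3) the between-clinic term is 0.0405, against 0.00375 for sampling within clinics. With unlimited patients per clinic, power would still be only Φ(√(0.27/0.0405) − 1.96) = 0.73.

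**Step 4: a 20-point effect and k=0.2 together, 120 per site.**

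| Pi0 to Pi1 | Power |
|---|---|
| 0.8 to 0.6 | 0.384 |
| 0.7 to 0.5 | 0.474 |
| 0.6 to 0.4 | 0.595 |
| 0.4 to 0.2 | 0.902 |

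**Step 5: the k implied by the stated clinic range.** If 95% of clinics lie within 15 points of 65%, then on a normal approximation k = (0.15/1.96)/0.65 = 0.118 before any gain from matching. At k=0.118 and 120 per site, the base case still has power above 0.999, but 0.8 to 0.6 falls from 0.851 to 0.751.

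**The case against.** The strongest reply is that the error is harmless. The 96% is too low for the planned size, so the trial is better powered on its own assumptions than it says. The UAG figure of more than 90% is true at 120 per site and stays true at k=0.2. The CAG figure of over 80% may refer to the k=0.2 row, printed as 0.82 even at 30 per cluster. All of this stands.

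It is also fair that k=0.3 is a stress value. With a mean of 0.65, it implies a 95% clinic range of 0.65 × (1 ± 1.96 × 0.3), about 0.27 to 1.03, far wider than the stated 50 to 80%. But the protocol chose to tabulate k=0.3 and then cited that table for robustness, so its result there has to be reported. The joint combinations in Step 4 are not in Appendix 6, which varies one quantity at a time. The CAG sentence names variability and effect size together, and reading that as a joint change is natural but is not the only reading.

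Four stronger readings are tempting, and the documents do not support them:

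- A reader might take 0.62, 0.63 and 0.66 as the power of this trial. They are for 30 per cluster; at 120 they become 85%, 90% and 95%.
- A reader might infer that any 20-point reduction with k=0.2 leaves the trial underpowered. From 0.4 to 0.2 the power is 90%; the low figures apply to baselines of 0.6 to 0.8.
- A reader might infer that k=0.10 is refuted by 0.118. The protocol's k is a matched value and 0.118 is unmatched; matching could account for the difference, although the protocol does not quantify that gain.
- A reader might suppose that j=30 is an effective size after a design effect. The appendix defines j only as the sample size per cluster.

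**Conclusion.** The power statement is wrong as written: 96% is the 30-per-cluster figure, and 120 per site gives above 99.9% in the base case. That error is in the safe direction.

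The two assurances are not demonstrated for the planned size by the appendix they cite, and they hold only in part when recomputed. They survive k=0.2 alone and the tabulated 20-point effects alone at k=0.10. They fail at the appendix's own k=0.3, and they fail by a wide margin when k=0.2 coincides with a 20-point reduction from a baseline of 0.6 to 0.8.

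The mismatch between 30 and 120 can be read off the page and needs no model. The recomputed figures rest on the inferred formula, two-sided alpha of 0.05, five complete pairs and full enrolment of 120 per site. The point calls for a correction of text and table. It does not show that the trial is too small on its main assumptions.

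**What to change.** 1. In section 3.2.5, replace 96% with above 99%, stated for 0.65 to 0.325, k=0.10, five matched clinics and 120 per site.
2. Rerun the Appendix 6 sensitivity rows at 120 per site and Pi0 = 0.65. Include k = 0.10, 0.118, 0.2 and 0.3, and rows in which k and effect size change together. Label 0.118 as the unmatched value implied by the 50 to 80% range. Name the formula and the sidedness of alpha.
3. Replace the general assurances for CAG and UAG with conditions: at k=0.10 the tabulated smaller effects keep power at 85% or more; at the base effect power stays above 80% for k up to about 0.25 and falls to about 70% at k=0.3; it falls well below 80% when a 20-point reduction from a baseline of 0.6 to 0.8 is combined with k=0.2.

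The cost is a text edit and one short rerun of the table. Some stated figures become less favourable. No change in enrolment or number of clinics follows from this point.

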## 3.2 Objective 2: To evaluate the effectiveness, efficiency, and health care quality of a differentiated system of care that includes targeted models of care.

Overall, this objective seeks to evaluate the effectiveness of a differentiated system of HIV care delivery in which the frequency, type, or intensity of contact with the health system is tailored to patient needs. The differentiated system of care includes targeted evaluation of three care models targeting patients stable on ART [community adherence groups (CAGs)], urban adherence groups (UAGs), and fast-track clinic visits), complemented by a model designed for HIV infected patients not yet on therapy (streamlined ART initiation (START)). An overview of these models is available in Appendix 4. These models will be implemented simultaneously, and will be evaluated using a common evaluation framework that includes effectiveness (with a primary outcome of retention), efficiency, and quality.

Patients who meet eligibility criteria, express willingness to participate, and provide written informed consent at the selected intervention sites will be enrolled. Interventions will be targeted by the type of site (rural/urban, high/low volume), baseline retention at site, and by patient status (treatment naïve vs experienced, stability on treatment).

### 3.2.1 Methodology for Objective 2

To evaluate the effectiveness, efficiency and quality of the differentiated care models, a matched cluster randomized design approach is proposed for the CAG and the UAG models, due to substantial weaknesses in existing regional observational pilot data in various settings. Cluster level analysis is being pursued as introduction of the intervention occurs at the clinic level. Randomization is being proposed to account for selection bias encountered in previous observational analyses. As there is little to no observational or implementation data for the Fast-Track and START models, and the goal is to generate such data in Zambia, a difference-in-difference design will be used to calculate the effect of the models on the outcomes of interest.

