### 3.2.2 Population

Inclusion criteria:

- HIV-positive adolescents and adults (> 14 years of age)
- Not acutely ill
- For CAGs, UAGs, and Fast-Track models: on ART for at least 6 months
- For the START model: ART naïve and meet the Zambian HIV guidelines for treatment initiation

Exclusion criteria:

- For CAGs, UAGs, and Fast-Track: CD4 < 200 in the last 6 months
- For CAGs, UAGs: Inability to participate in the group activities due to cognition deficits or mental illness.
- Unable to provide consent or unwilling to participate in study
- Pregnancy

###

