### 3.2.4 Measurements

We will use information from routine clinical documentation, which includes:

1. Socio-demographic, laboratory, clinical, and pharmacy data

We will extract standard de-identified socio-demographic, laboratory and clinical data for all patients (intervention and control) from the patient’s electronic medical records.

1. Participant attendance, individual ART pick-up, and symptom assessment for UAG, CAG, and Fast-Track

We will use model specific registers that include information such as 1) Attendance, 2) Receipt of medications 3) Symptom checklist 4) Whether patient prefers to remain in care model or return to standard clinical care. This information will be entered into the study database using a tablet.

In addition, the study will also measure additional processes and outcomes related to each of the four models of care, which includes:

1. Movement between tiers for UAG, CAG and Fast-Track

The presence of symptoms or a patient’s desire to return to standard care will trigger an up-referral to the facility. Patients with acute illness, once stabilized, will be down-referred back to the model. Movement between tiers will be measured using a register that will document any up-referral after initial study enrollment. This information will be entered into the study database using a tablet. Down-referrals will be captured by measuring assigned frequency of clinic visit in the electronic medical record.

1. Patient satisfaction and patient-centeredness for UAG, CAG and Fast-Track

Patient satisfaction and centeredness will be measured as part of a semi-structured patient-exit survey that will be conducted after the 12-month intervention period.

1. Viral load testing

Viral load testing (at baseline and exit) using dried blood spot specimens will be conducted as noted in the procedures section.

1. Costing

A semi-structured costing questionnaire will be administered to a subset of intervention participants to assess direct and indirect health costs of the intervention (as noted in the procedures section). In addition, to calculate the resource use of each activity, we will use time-in-motion studies among patients and health care workers prior to and during the intervention.

1. Process data will be collected through qualitative assessments (i.e. HCW interviews during and at the end of follow-up period) and facility-level assessments (i.e. frequency of pharmacy stock outs).

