### 3.2.5 Analytic Approach and Sample Size Considerations

*a. Outcomes and Analysis*

The primary outcome in three models that target retention in care (CAG, UAG, Fast-track) is defined as time to first missed pharmacy pick-up (> 7 days late). For the START model which targets ART initiation, we use the date of ART initiation as the primary outcome. To evaluate the impact of CAG and UAG interventions, we will use Kaplan-Meier estimates of time to the primary outcome, stratified by intervention condition, using log rank tests. For Fast-track and START, our primary analysis will take a difference-in-difference approach in which we estimate the difference in the change in the rate of the outcome between intervention and control settings. In secondary analyses of the primary outcome, we will explore longer intervals of lateness that comprise a missed pharmacy visit (14 and 30 days) as well as adjustment for baseline patient characteristics. We will also explore analysis using medication possession ratio (MPR) as the outcome and other metrics of retention ^17^ that incorporate both frequency of missed visit as well as interval of time before return.

The secondary outcomes will focus on implementation and quality (see Appendix 2).

a. *Implementation Outcomes*

- *Feasibility* will be evaluated qualitatively through analysis of interviews and focus groups.
- *Costs* will be evaluated quantitatively using “bottom-up” activity-based micro-costing techniques (see Measurements section above) and “top-down” evaluation of budgets and spending reports, based on calculations of DALY’s.
- *Fidelity* of the intervention models will be assessed through estimates of the proportion of identified and eligible patients successfully enrolled in a model, the proportion of missed visits, and the proportion of CAG/UAG still functioning at the end of the 12-month intervention period.

*b. Quality Outcomes*

We use the framework offered by the Institute of Medicine to define quality outcomes.:

- *Access* will be evaluated using time (days) from positive symptom screen to appropriate referral.
- *Efficiency* will be assessed using cost-effectiveness analysis. We will consider the incremental cost per additional patient retained and the cost per death averted using effectiveness data from each model.
- *Safety* will be evaluated by estimates of the proportion of patients with appropriate laboratory monitoring and symptom screening.

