No control patients will be actively enrolled in START and Fast Track sites. We will use routinely collected, de-identified, aggregated data to evaluate the primary outcome of retention (Fast Track) and days to ART initiation (START).

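### The Fast-Track primary outcome is assigned to aggregated routine data, contrary to the protocol's own patient-level provisions, and no common eligible population is set for the difference-in-difference

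*Protocol*

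**What the plan says.** On the form of the data, the last paragraph of Protocol section 3.2.5 states "No control patients will be actively enrolled in START and Fast Track sites" and then "We will use routinely collected, de-identified, aggregated data to evaluate the primary outcome of retention (Fast Track". It does not say whether aggregates serve the control clinics only or all four.

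Three other places assume patient-level data:

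- Section 3.2.4: "We will extract standard de-identified socio-demographic, laboratory and clinical data for all patients (intervention and control", taken from the electronic medical record.
- Section 3.2.5, outcomes: "The primary outcome in three models that target retention in care (CAG, UAG, Fast-track) is defined as time to first missed pharmacy pick-up", meaning more than 7 days late. Secondary analyses use 14 and 30 days, medication possession ratio and adjustment for baseline characteristics.
- Section 3.2.5, sample size: "Our target sample size for Fast-track is 200 patients at each of four sites (two intervention sites and two control sites; n=800 total".

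On who is enrolled, section 3.2.2 requires "For CAGs, UAGs, and Fast-Track models: on ART for at least 6 months" and excludes "For CAGs, UAGs, and Fast-Track: CD4 < 200 in the last 6 months". It also excludes acute illness, pregnancy and unwillingness. Section 3.2 adds: "Patients who meet eligibility criteria, express willingness to participate, and provide written informed consent at the selected intervention sites will be enrolled".

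The primary Fast-Track analysis is a difference-in-difference between intervention and control settings. Adjustment appears only among the secondary analyses. Section 1.6 caps enrolment at each intervention clinic and leaves the remaining patients on standard care.

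**The concern.** A difference-in-difference needs four cells: intervention and control, before and after. It removes a difference between clinics that stays constant. It does not remove a change in the kind of patient measured when that change happens at the intervention clinics alone. The protocol describes only one cell, the enrollees after the start. It does not say which patients form the other three, and it assigns the outcome to a form of data from which ordinary clinic totals would not give an individual's first late pick-up.

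The protocol treats this problem seriously elsewhere. Its literature review faults earlier adherence-group studies for lacking a comparable stable comparator. Section 3.2.3 has eligible CAG and UAG control patients approached about their willingness to take part. Fast-Track has no equivalent step. At stake is the primary Fast-Track estimate, which could be inflated or diluted depending on how the data sentence is carried out.

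**Working it through.** **1. The protocol's own figures.** 200 × 4 sites = 800 patients. The anticipated fall is 80% − 40% = 40 points, with stated power of 80%. No intracluster correlation or coefficient of variation is given for Fast-Track, so that power cannot be confirmed. Without clustering, 400 against 400 gives more than 99.9%. Power of 80% is reached at a correlation of about 0.085 (two groups) or 0.052 (four-cell difference-in-difference). The present point does not depend on the power figure.

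**2. The provisions side by side.**

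| Provision | Needs patient rows? | Met by clinic totals? |
|---|---|---|
| Time to first pick-up more than 7 days late | yes | no |
| 14- and 30-day variants, possession ratio | yes | no, unless each is computed before aggregation |
| Adjustment for baseline characteristics | yes, or stratified counts | no |
| 200 patients per control site | a defined patient set | no |
| Eligibility applied to controls and to the before period | yes, or filtering before aggregation | no |

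**3. Reading A: clinic-wide before, enrollees after.** Assume no true effect, the planning 80% in the intervention before cell and in both control cells, and underlying lateness e among enrollees.

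Spurious effect = (e − 80) − (80 − 80) = e − 80.

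- e = 75% (assumed): −5 points, and 5/40 = 12.5% of the anticipated effect.
- e = 70% (assumed): −10 points, and 10/40 = 25%.

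An observed fall of 40 points would then contain a true effect of 35 or 30.

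**4. Reading B: clinic-wide aggregates at all four clinics.** Enrolment is capped at 200 per clinic, so the clinic-wide effect = 40 × 200/N. The protocol gives no N. For assumed N of 1,000 to 3,000 ART patients, this is 40 × 200/1,000 = 8.0 points down to 40 × 200/3,000 = 2.7 points.

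**5. Reading C: the same kind of patient before and after in each setting.** With enrollee risk e in both periods and no effect, (e − e) − (80 − 80) = 0. The fixed part cancels. A different trend among willing patients would remain.

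**The case against.** Section 3.2.4 already provides for record extraction from control patients. Age, time on ART and CD4 can be filtered there, or before counts are aggregated. A reader might infer from section 3.2.5 that the control data cannot be restricted to comparable patients. The documents do not support that: the restriction is possible but unspecified, and the sections disagree.

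A reader might also infer that the Fast-Track estimate will necessarily be biased. That does not follow either, because the before population is undefined and Reading C removes the fixed part. Under Reading B the error runs the other way.

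A third inference is a bias of up to 20 points, from the statement in section 1.1 that about 50% of patients are stable. That share is not the eligible share. The criteria in section 3.2.2 are broader, and section 3.2.3 keeps Fast-Track participants whose baseline CD4 proves to be below 200 or whose viral load is above 1,000. With a 50% share and a risk ratio of 0.6, lateness in the remaining patients would be 0.80/(0.5 × 0.6 + 0.5) = 100%, which is an arithmetic ceiling. With an assumed eligible share of 80%, eligibility alone could not lower risk below (0.80 − 0.20 × 1.00)/0.80 = 75%, a bias of at most 5 points. Selection by willingness comes on top and cannot be sized from the documents. The 80% may also already describe the target patients.

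Finally, Fast-Track is openly observational, and cohort definitions are often left to an analysis plan. That is fair for detail. But the protocol itself fixes the form of the data: an analysis plan using patient rows would contradict the last paragraph of 3.2.5, and one using clinic totals would contradict 3.2.4 and the outcome definition. That part of the concern stands.

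**Conclusion.** The concern holds as a contradiction with consequences for a primary outcome. Section 3.2.5 assigns Fast-Track retention to aggregated data without enrolled controls, while 3.2.4 and other parts of 3.2.5 require patient-level data on control patients. No section applies the recordable eligibility criteria to the control or pre-intervention data.

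The size depends on the reading. Under Reading A the spurious fall is 5 or 10 points of 40, resting on assumed enrollee risks of 75% and 70%, on clinic-wide lateness of 80%, and on enrollees being the less late patients. Under Reading B the effect is diluted by an amount that depends on clinic size, which the protocol does not give. Under Reading C the fixed bias is zero, but the text does not provide for that design. Willingness and consent cannot be recovered from routine control data under any reading, so some selection remains in any comparison that uses enrollees only.

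**What to change.** Reword the last paragraph of section 3.2.5 so that Fast-Track uses de-identified patient-level SmartCare data, as 3.2.4 states. If only aggregates are permitted, have the counts produced after filtering.

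Define one cohort and apply it identically in all four cells: older than 14 years, on ART at least 6 months at an index pick-up, no CD4 below 200 in the prior 6 months, not pregnant. State the pre-period, and use the same more-than-7-days outcome over 12 months in each cell.

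Report two comparisons together:

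- All eligible patients at all four clinics. This is like for like, with dilution by non-enrolled patients acknowledged.
- Enrollees against the eligible control cohort, adjusted for age, sex, time on ART and prior lateness where available, with residual selection by willingness acknowledged. Patients with 6 to 11 months on ART have no full prior year, so adjustment for prior lateness will be incomplete.

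The enrollee comparison should not stand alone as the primary contrast, because that would bring willingness selection back in. The cost is reworded text, one extra SmartCare query and possibly an ethics notification for patient-level data at the control clinics. No control enrolment is needed.
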